# Protocol for the MyPREPED trial: hybrid type 2 effectiveness–implementation trial of a peer-delivered digital self-management tool (MyBRANCHES) for young people in Australia transitioning from early intervention in psychosis services

**DOI:** 10.1192/bjo.2026.12056

**Published:** 2026-07-27

**Keywords:** Early psychosis, peer support, self-management, digital mental health, discharge

## Abstract

**Background:**

Peer-supported self-management at discharge from early intervention in psychosis services (EIPS) has received limited attention. The MyPREPED (My Personal Recovery Plan for Early Discharge) trial will evaluate a co-designed, digital and paper-based, peer-delivered recovery and self-management focused intervention, tailored for young people exiting EIPS.

**Aims:**

This protocol describes a hybrid type 2 effectiveness–implementation trial designed to assess MyPREPED’s impact, feasibility, real-world implementation and cost–utility.

**Method:**

This multi-site, mixed-method, two-arm (1:1), parallel-group, randomised controlled trial (MyPREPED versus treatment as usual) trial will be delivered across eight Australian EIPS that deliver ultra-high risk and/or first-episode psychosis streams, using a hybrid type 2 implementation–effectiveness design. Eligible participants are young people aged 16 years and over within 6 months of planned discharge from EIPS. Peer coaches will deliver up to ten sessions of using a self-management plan (modules: discharge, recovery, well-being, relapse prevention, goal-setting, service navigation). Co-primary outcomes include (a) mental health recovery (Recovery Assessment Scale – Domains and Stages; effectiveness outcome) and (b) feasibility (Feasibility of Implementation Measure; implementation outcome). Secondary outcomes assess broader effectiveness domains (mental health quality of life, clinical and functional outcomes) and other implementation outcomes. A cost–utility analysis will estimate incremental costs and quality-adjusted life-years associated with MyPREPED, alongside a secondary cost-effectiveness analysis. Analyses will follow intention-to-treat principles, using mixed-effects models.

**Conclusions:**

This study will provide the first rigorous test of a co-designed, peer-delivered recovery and self-management focused intervention specifically targeting EIPS discharge.

Treating psychosis and associated disorders as early as possible is regarded as best practice in mental health services globally because of the positive impacts this can have on an individual’s clinical and functional outcomes.^
1
^ The large evidence base for early intervention has led to the establishment of specialist mental health services known as early intervention in psychosis services (EIPS), which provide multidisciplinary, multimodal interventions focused on people aged approximately 12–25 years who are at risk of, or have experienced, a first episode of psychosis. Their goals are to prevent psychosis where possible, reduce the duration of untreated psychosis, restore usual functioning and minimise the impact on families. EIPS are designed to intervene during the ‘critical period’, when treatment is most likely to deliver long-term benefits and when supportive social structures can be mobilised for recovery.^
2
^

In Australia, EIPS are funded through two parallel systems.^
3
^ State-funded teams are embedded in local health districts (e.g. 19 teams across 17 sites in New South Wales)^
4
^ primarily provide care to young people experiencing a first episode of psychosis (FEP). In parallel, federally funded youth mental health services (headspace) operate more than 100 centres nationally; a subset of these centres deliver specialised early psychosis programmes using an Early Psychosis Prevention and Intervention Centre (EPPIC)-aligned model to young people. These programmes support young people with an FEP, who typically receive care for 2–5 years, as well as those identified as being at ultra-high risk of developing psychosis, who are supported for up to 12 months within dedicated ultra-high risk streams. As of 2025, 14 headspace-based early psychosis programmes are operating nationally, with further expansion underway. Across both funding models services typically include medication, psychological therapies, psychoeducation and assistance with education, employment and family support, although local resources determine the scope of delivery.^
5–7
^ Similar early intervention models for psychosis are implemented internationally, including EIPS in the UK, coordinated specialty care programmes in the USA and established early psychosis services across Europe (e.g. in Scandinavia, The Netherlands, Italy and Spain).

## Transition from EIPS as a critical failure point

Although EIPS have demonstrated significant short-term benefits in clinical and functional outcomes,^
1,^
^
2
^ transitions in care such as discharge from EIPS, especially into adult or lower-intensity care, remains a key service gap, and may partly be why early gains might be lost over time. Australian epidemiological evidence indicates that young people exit EIPS into markedly different care pathways. In a state-based cohort from Melbourne, 37% of young people were discharged to adult mental health services, whereas 63% transitioned to lower-intensity care, including primary care (46.3%), private psychiatry (11.7%) and private psychology (5.4%).^
8
^

Qualitative research in Australia highlights how these transitions are experienced by young people and families. Entry into services, staff turnover, hospital admission and discharge, and transition out of EIPS are described as disrupting continuity of care.^
4,9
^ EIPS discharge is reported as abrupt and undersupported, leaving young people to navigate the adult mental health system alone at a critical stage. Following discharge, young people can enter a period of heightened vulnerability, with increased risks of relapse, readmission and disengagement from care, which can adversely affect long-term mental health, educational, employment and social outcomes.^
10
^ Internationally, emerging pilot evidence suggests that structured coaching interventions delivered by clinicians to support transition from EIP services may improve functioning outcomes compared with historical controls.^
11
^

Together, these findings indicate substantial variability in post-EIPS care pathways and suggest that heterogeneity in discharge destinations may contribute to uneven continuity and support during a critical period, underscoring the need for more coordinated transition interventions.

## Peer-supported self-management

Self-management interventions supported by peer support workers (also called peer workers, or as in this trial, peer coaches) offers a potential strategy to address these gaps. Key elements of self-management interventions for serious mental health conditions include psychoeducation, relapse prevention, learning coping strategies, personal recovery and goal-setting, and can also extend to behavioural tailoring to facilitate medication adherence.^
12
^ Peer support is defined as ‘support or services provided to people with mental health problems by other people who have experienced mental health problems themselves’.^
13
^ In mental health services, peer support workers constitute one of the fastest-growing components of the mental health workforce internationally.^
14
^ In Australia, although peer support workers remain a minority relative to the established clinical workforce, the number of paid peer support workers in specialised mental healthcare facilities increased by an average of 18% per year between 2017–2018 and 2021–2022.^
15
^ This growth rate outpaced that of many traditional professional groups, including psychiatrists, nurses and psychologists. Systematic review evidence of the effectiveness of peer support is mixed, but benefits have been observed for self-reported recovery outcomes.^
13,16
^ Trial evidence suggests that peer support delivered in conjunction with structured approaches, such as recovery or self-management planning, may be associated with improved outcomes such as reduced readmission rates.^
17,18
^

The Crisis Resolution Team Optimisation and Relapse Prevention (CORE) randomised controlled superiority trial in the UK demonstrated that at 1-year follow-up, peer-delivered self-management planning following crisis care had significantly lower readmission rates compared with self-management alone (29 *v*. 38%; odds ratio 0.66, 95% CI 0.43–0.99), although the confidence intervals were relatively wide.^
18
^ The associated trial-based economic evaluation suggested the peer-delivered self-management intervention would likely be cost-effective.^
19
^ The results point to the potential for peer-delivered self-management planning to reduce readmission rates. Since the CORE trial, the self-management resource has been adapted into a digital tool for use in Australian community mental health services through co-production.^
20
^

## Need for digital, co-produced solutions

Despite recommendations for use in clinical guidelines^
21
^ and systematic review evidence of its effectiveness for serious mental illness,^
12
^ structured self-management planning remains inconsistently implemented in EIPS.^
22
^ Discharge processes are variable, often clinician-driven and rarely personalised, and support is unable to be sustained after leaving a service. Digital delivery provides a flexible means to extend support beyond clinical contact time, is acceptable and engaging for young people, and can integrate self-management planning into routine during and after discharge.^
23
^ At the same time, the peer workforce is recognised as a critical enabler of engagement and empowerment in youth mental health services,^
24
^ yet remains underutilised in supporting transitions out of EIPS.^
4
^ Further to this, evidence from systematic reviews and emerging studies indicates that digital interventions alone often achieve limited engagement and clinical impact unless complemented by human support,^
25–27
^ with preliminary evidence suggesting human involvement can enhance adherence, therapeutic alliance and outcomes in digital mental health interventions (including for psychosis spectrum disorders). This reinforces the need for relational contact alongside digital delivery to optimise engagement and effectiveness in youth services.

Overall, these findings highlight the need for structured, personalised and youth-tailored support during transitions out of EIPS. Self-management interventions are associated with improvements in clinical, functional and service use outcomes such as readmission rates, while peer support workers can enhance engagement and promote recovery. Digital delivery offers a flexible mechanism to extend support beyond traditional service boundaries; however, evidence indicates that digital interventions are most effective when embedded within relational models of care that include human support. The My Personal Recovery Plan for Early Discharge (MyPREPED) trial integrates structured self-management planning, peer-led support and digital delivery to address the well-documented gap in transitional care for young people exiting EIPS.

## The MyPREPED trial and development work

The MyPREPED trial will evaluate a co-designed, digital, peer-delivered self-management intervention co-adapted for young Australians being discharged from EIPS. The trial intervention (MyPREPED) will be delivered by a peer coach, employed in EIPS sites, using the co-designed self-management tool called My Building Recovery and Navigating Changes with Peer Helpers in Early Intervention Services (MyBRANCHES), which will be available via a progressive web app (enabling secure access across smartphones, tablets and desktop devices without requiring installation from commercial app stores to enable more equitable access) or a paper-based version depending on the participant preference. An overview of modules within the MyBRANCHES tool and their associated goals are presented in Fig. 1.

**Fig. 1 f1:**
[figure not shown]
Fig. 1 long description. MyBRANCHES homepage modules and associated goals. MyBRANCHES, My Building Recovery And Navigating Changes with Peer Helpers in Early Intervention Services.

The MyBRANCHES tool has been built through a programme of iterative co-design. A co-designed, paper-based self-management tool, adapted for use in partnership with peer workers in the UK,^
28
^ was found to be effective at reducing readmission rates in a crisis discharge setting.^
18
^ More recently, we demonstrated the preliminary acceptability and usability of a co-produced digital version of the self-management tool among adults with severe mental illness, with personalisation, customisation, language, flexibility of use and peer support being key themes.^
20
^ These studies have informed the current youth version’s development of the tool, renamed through co-design as MyBRANCHES.^
29
^

Given the limited evidence base for structured, personalised self-management tools in psychosis, particularly those tailored to the discharge transition out of EIPS, there is a need to evaluate not only the clinical effects of the MyPREPED intervention (i.e. up to ten sessions of peer coaching with the MyBRANCHES tool alongside standard discharge care), but also how it can be feasibly and sustainably integrated into routine EIPS delivery. A hybrid type 2 implementation–effectiveness design^
30,31
^ was therefore selected to enable simultaneous examination of clinical outcomes, implementation processes and contextual determinants influencing real-world uptake. The specific aims of the study are outlined below.

## Aims and research questions

### Aim 1: Experimentally evaluate the effects of MyPREPED versus usual care (control)

We aim to evaluate the impact of the MyPREPED intervention, on mental health recovery alongside other outcomes relating to mental health quality of life, and psychosocial and functional outcomes (see section ‘Outcomes’), by asking the following questions:Is MyPREPED more effective than usual care in improving mental health recovery at the primary end-point (12 weeks post baseline)?Is MyPREPED more effective than usual care in improving secondary outcomes at the primary end-point (12 weeks post baseline)?Are effects maintained at 52 weeks post baseline?

### Aim 2: Evaluate the implementation of MyPREPED in routine EIPS settings

We aim to examine implementation outcomes, including feasibility, acceptability, appropriateness, adoption, fidelity, penetration, retention, sustainability and scalability of MyPREPED, using mixed methods, by asking the following questions:Is MyPREPED feasible to implement in real-world EIPS settings, as assessed with the Feasibility of Intervention Measure (FIM) and complementary feasibility indicators?Is MyPREPED acceptable and appropriate to young people, peer coaches and clinicians?What are the levels of adoption, fidelity, penetration and retention across participating services?How usable is the MyBRANCHES tool for young people and peer coaches?What implementation barriers, facilitators, and contextual determinants influence sustainability and scalability?What practical, operational and contextual lessons can be learned from implementing the trial across sites?

### Aim 3: Evaluate the economic impact of MyPREPED

We aim to evaluate the cost-effectiveness of the MyPREPED intervention relative to usual care, from both health sector and societal perspectives through cost–utility analyses, by asking the following questions:Is MyPREPED cost-effective compared with usual care alone from societal and health sector perspectives at 12 weeks post baseline, using utility values (derived from the Recovering Quality of Life 20-item measure (ReQoL-20))?Is MyPREPED cost-effective compared with usual care alone from societal and health sector perspectives at 52 weeks post baseline, using utility values derived from the ReQoL-20?Is MyPREPED cost-effective compared with usual care alone from societal and health sector perspectives at 12 and 52 weeks post baseline, using utility values derived from the 12-Item Short Form Health Survey (SF-12) as the Short Form 6-Dimension health utility measure (SF-6D)?

## Method

### Frameworks guiding the phased development of the tool, co-production and partnering with consumers

The development of the MyPREPED intervention was guided by a coordinated multi-framework approach to co-production and development of complex interventions,^
20
^ recognising that no single framework is sufficient for designing, adapting and implementing complex psychosocial interventions in real-world mental health systems.^
32
^ Consistent with the updated Medical Research Council Framework of developing, testing, evaluating and implementing complex interventions,^
33
^ the tool was iteratively co-produced through cycles of co-design, feasibility testing and refinement, to ensure clear mechanisms of action and alignment with youth and peer coach needs. Co-production principles shaped all stages of development, embedding lived, learned and practice-based expertise into the content, structure and delivery and evaluation (co-planning, co-design, co-delivery, co-evaluation).^
34
^ This included co-production of areas such as study design, implementation plans, training and outcomes. A Guidance for Reporting Involvement of Patients and the Public (GRIPP2) short-form^
35
^ table is provided in Supplementary File 1, outlining the roles of lived-experience partners in the development of the intervention. To maximise implementation potential within routine EIPS, we have selected to use the Consolidated Framework for Implementation Research (CFIR 2.0^
36
^) to examine the contextual determinants and service readiness, and Proctor’s implementation outcomes taxonomy to guide the specification of constructs such as acceptability, feasibility, fidelity, adoption and sustainability.^
37,38
^ Further, the MyPREPED trial’s hybrid type 2 design^
30
^ reflects this integrated approach to testing effectiveness and implementation. Together, this design and complementary frameworks provide a structured and transparent approach to developing, evaluating and interpreting the effectiveness, implementation and scalability of MyBRANCHES within diverse youth psychosis services.

### Design

This is a multi-site, two-arm (1:1), parallel-group, randomised controlled trial of MyPREPED versus standard discharge transition care. Both groups receive standard EIPS care. We will use a hybrid type 2 implementation–effectiveness design aligning with the current Standard Protocol Items: Recommendations for Interventional Trials (SPIRIT) statement^
39
^ and Consolidated Standards of Reporting Trials (CONSORT) guidance.^
40
^ This hybrid type 2 trial has co-primary outcomes: implementation feasibility (measured with the FIM)^
41
^ and recovery (measured with the RAS-DS).^
42
^

### Setting

The study sites are planned to include eight community-based EIPS located in New South Wales, Victoria and Queensland, Australia. Sites comprise services from four of the federally funded multidisciplinary FEP and ultra-high risk headspace services (Western Sydney, New South Wales; Metro Brisbane area, Queensland) and four state-funded services in metropolitan areas of Sydney (New South Wales), Melbourne (Victoria) and Brisbane (Queensland). Contextual variation across state-funded and federally funded EIPS (e.g. peer workforce maturity, staffing models, discharge processes) will be documented with CFIR-informed site profiles. These contextual data will support interpretation of effectiveness and implementation outcomes in line with SPIRIT guidance.

### Participants

Participants must meet the following inclusion criteria: aged 16 years or over, registered with a participating EIPS and approaching discharge (within 6 months), and able to understand English. Exclusion criteria include lack of capacity to consent, as judged by the clinical team; and at high risk that study participation would be unsafe, as judged by the clinical team. Figure 2 presents the planned participant flow through enrolment and allocation, and details the intervention components and follow-up time points. A CONSORT flow diagram is provided in Supplementary File 2.

**Fig. 2 f2:**
[figure not shown]
Overview of intervention and participant flow. EIPS, early intervention in psychosis services; MyBRANCHES, My Building Recovery And Navigating Changes with Peer Helpers in Early Intervention Services; MyPREPED, My Personal Recovery Plan for Early Discharge.

### Recruitment and consent

Potential participants will be identified by EIPS clinicians as they approach discharge and are referred to the research team. The team will provide study information (via a Participant Information Statement and an e-consent platform) and obtain written or electronic informed consent before conducting baseline assessments (online, via digital conferencing, face to face or via phone per participant preference)^
43
^ and randomisation. Additional verbal consent before any qualitative interviews will be obtained and formally recorded.

### Randomisation and blinding

Randomisation will be performed centrally with the REDCap randomisation module, with permuted blocks of random size (2, 4) and stratification by site and caseload type (FEP versus ultra-high risk). Allocation will be concealed from outcome assessors and statisticians. Participants and peer coaches cannot be blinded to allocation, but assessors will complete a blinding questionnaire post intervention, and any suspected breaches will be documented for sensitivity analyses.

### Pilot

Before full implementation, a small pilot phase will be undertaken to assess the feasibility and acceptability of recruitment, intervention delivery and study procedures within participating EIPS settings, with pilot participants rolled into the full trial sample unless major feasibility or safety concerns are identified.

### Intervention: MyPREPED

The MyPREPED intervention is described in accordance with the Template for Intervention Description and Replication (TIDieR) checklist^
44
^ to support replication (Table 1). MyPREPED is a complex, peer-delivered, self-management and discharge-planning intervention delivered by trained lived-experience peer coaches, using the MyBRANCHES self-management tool. MyPREPED comprises two integrated components: (a) structured peer-coaching sessions and (b) guided use of the MyBRANCHES tool, delivered in digital or paper-based format according to participant preference.

**Table 1 tbl1:** TIDieR checklist for MyPREPED Table 1 long description.

TIDieR item	Description of MyPREPED intervention
1. Brief name	MyPREPED, a peer-delivered self-management and discharge-planning intervention for young people transitioning from EIPS. The self-management tool used is called MyBRANCHES. MyPREPED comprises the combined delivery of peer-coaching sessions and guided use of the MyBRANCHES self-management tool.
2. Why (rationale)	Designed to improve discharge outcomes by providing structured self-management, personalised recovery planning and lived-experience support during the transition out of EIPS.
3. What (materials)	Materials include the MyBRANCHES tool (digital and paper-based options available), peer coach manual, fidelity checklists, training modules (2-day workshop online content), supervision guides and logic model. The digital component is a PWA, which uses responsive design allowing flexible access and device-agnostic use, supporting implementation for diverse preferences. The MyBRANCHES tool is versioned, with updates documented across the trial period, and participants retain access to their materials following discharge. The digital tool is gently gamified (avatar, customisation options) and allows optional sharing with families/clinicians. All materials will be openly available via the OSF.
4. What (procedures)	Sessions follow a standard structure: brief check-in, collaborative selection of MyBRANCHES modules, guided completion of modules and agreement on next steps. Modules include discharge planning, recovery planning, well-being planning, relapse-prevention planning, crisis planning, goal-setting, coping strategies, psychoeducation and lived-experience examples. Peer coaches document session content, delivery mode and duration in logbooks. Any safety concerns identified during sessions are managed in line with prespecified risk escalation protocols and communicated to the research and clinical care team as required. Fidelity is monitored through checklists and supervision review.
5. Who provides	Delivered by trained lived-experience peer workers (‘peer coaches’) employed by participating services. The term for their role here was chosen as ‘peer coaches’ by the lived experience advisory group. Peer coaches typically hold a Certificate IV in Mental Health (or equivalent), have experience in psychosis/mental health settings, and complete formal MyPREPED training and safety procedures. Ongoing competency is supported through monthly supervision and review of session checklists for fidelity. Monthly group supervision is provided by study investigators.
6. How (mode of delivery)	One-to-one peer-coaching sessions delivered face to face, by telephone or via telehealth. Participants may use digital or paper versions of MyBRANCHES. Engagement strategies include flexible scheduling, multimodal delivery and brief between-session check-ins.
7. Where	Delivered in routine EIPS settings or remotely (telephone/telehealth) depending on participant preference and service context.
8. When and how much (dose)	Up to ten sessions of approximately 45–60 min each. Minimum effective dose defined as three or more sessions for per-protocol analyses. Sessions generally commence within 12 weeks before anticipated discharge, with timing adjusted based on clinical trajectory and participant preference.
9. Tailoring	Tailoring occurs jointly between peer coach and participant. Elements tailored include module prioritisation, pacing, scheduling, delivery format (digital or paper), modality (in person/telephone/video-conferencing), session frequency (weekly/fortnightly/tapering) and involvement of family/clinicians. Content and delivery are also tailored youth preferences (e.g. access to a non-gamified version).
10. Modifications	Any adaptations during feasibility testing will be documented following CONSORT-SPI and SPIRIT guidelines, with approval by the study governance group and documentation of rationale.
11. How well (planned fidelity assessment)	Fidelity monitored through peer coach logbooks, structured fidelity checklists and monthly supervision reviews. Fidelity assessments are conducted by trained members of the research team. Deviations and contextual adaptations will be recorded.
12. How well (actual fidelity)	To be reported post trial, including adherence to core components, dose delivered and received, mode of delivery and participant engagement patterns.
Fixed (prespecified) components	Core MyBRANCHES modules (discharge planning, recovery planning, well-being planning, relapse-prevention, crisis planning, and goal-setting); structured session flow (check-in, module selection, guided use, next steps); standardised training package; peer coach role requirements; fidelity monitoring procedures; session documentation requirements; maximum dose (up to ten sessions); core safety and risk-management procedures; availability of digital and paper materials; open-science access to manuals and tools.
Adaptable (flexible) components	Module prioritisation based on participant goals; mode of delivery (in person/telephone/telehealth); format (digital or paper workbook); session frequency (weekly/fortnightly/tapering); scheduling and pacing; optional between-session check-ins; extent of family/clinician involvement; commencement timing relative to discharge; culturally or contextually relevant examples used by peer coaches; tailoring to local service workflows and participant preferences.

TIDieR, Template for Intervention Description and Replication; MyPREPED, My Personal Recovery Plan for Early Discharge; MyBRANCHES, My Building Recovery And Navigating Changes with Peer Helpers in Early Intervention Services; EIPS, early intervention in psychosis services; PWA, Progressive Web Application; OSF, Open Science Framework; CONSORT-SPI, Consolidated Standards of Reporting Trials – Social and Psychological Interventions; SPIRIT, Standard Protocol Items: Recommendations for Interventional Trials.

MyPREPED includes both fixed (prespecified core components) and flexible (personalised) elements, which are fully detailed in Table 1. A logic model and description of active ingredients are provided in Supplementary File 3. Content overview and interface are provided in Supplementary Files 4 and 5, respectively.

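### As written, enrolment can open 26 weeks before discharge and sessions start 12 weeks before it, so the 12-week co-primary assessments can precede adequate treatment, or any treatment

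*Protocol article*

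**What the plan says.** All references are to the protocol article.

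- **Entry.** The Abstract (Method) makes people eligible "within 6 months of planned discharge from EIPS", and the Participants section repeats the 6-month limit. Recruitment and consent says that candidates are "identified by EIPS clinicians as they approach discharge" and that the team will "obtain written or electronic informed consent before conducting baseline assessments" and randomisation. Neither that section nor Randomisation and blinding gives an interval to the first session.
- **Start of treatment.** Table 1, item 8: "Sessions generally commence within 12 weeks before anticipated discharge, with timing adjusted based on clinical trajectory and participant preference". The adaptable components at the end of Table 1 include "commencement timing relative to discharge". The fixed components contain no start rule, and the text after the table says that Table 1 gives the fixed and flexible elements in full.
- **Dose.** Table 1 allows up to ten sessions, at weekly, fortnightly or tapering frequency. Three or more is the minimum effective dose for the per-protocol analyses.
- **Assessment.** Aim 1 and Outcomes put the primary RAS-DS end-point 12 weeks after baseline. FIM is collected at 12 weeks from intervention participants and peer coaches, and Table 2 shows no other FIM time point. The 12-week column of Table 2 is headed Post-intervention.

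**The concern.** Two clocks are in use. The primary end-point runs from baseline, while the usual start of treatment runs back from discharge. Nothing in the article joins them, and the entry window (about 26 weeks) is longer than the usual treatment lead time (12 weeks) plus the follow-up to the primary end-point (12 weeks). A site can follow every stated window and still assess someone before the first session.

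Two things are at stake. The 12-week RAS-DS difference would average over people with little or no exposure, for reasons of scheduling and not of choice or uptake. And FIM, a co-primary outcome with a single time point, could be rated by participants who have not yet met a peer coach.

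**Working it through.** **Reproducing the plan's sample size.** Inputs from Sample size and power: 7 points, SD 15, 20% attrition, ICC 0.02, cluster size 20. The article does not state alpha or power; two-sided 0.05 and 80% are assumed here.

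- Two-sample t calculation: 73.05, so 74 per arm.
- Design effect: 1 + (20 − 1) × 0.02 = 1.38.
- 74 × 1.38 / 0.80 = 127.7, so 128 per arm and 256 in total (258 if rounded up at each step). The stated 260 is consistent with 80% power.

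**Dates.** Let T be weeks to discharge at baseline, with the first session at the earliest usual point, 12 weeks before discharge. The first session then falls max(0, T − 12) weeks after baseline.

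- T = 26: 26 − 12 = week 14, two weeks after the primary assessment.
- No session by week 12 if T − 12 > 12, that is T > 24.
- Three weekly sessions need the first by week 12 − 2 = 10, so fewer than three if T > 22.
- Three fortnightly sessions need the first by week 12 − 4 = 8, so fewer than three if T > 20.

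A start 8 weeks before discharge also lies within the usual window. It lowers these limits to T > 20, 18 and 16.

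**The column label.** Ten fortnightly sessions span 9 × 2 = 18 weeks, so the 12-week visit is not post-intervention for someone who uses all ten at that pace, even with an immediate start. Ten is a ceiling, so this applies only to such users.

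**Illustration of size.** The article gives no distribution of T. Suppose that T is uniform over 0 to 26 weeks and that everyone waits for the earliest usual start:

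- No session: 2/26 = 7.7%.
- Fewer than three weekly sessions: 4/26 = 15.4%.
- Fewer than three fortnightly sessions: 6/26 = 23.1%.

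With T uniform over 0 to 24 weeks, the shares are 0%, 8.3% and 16.7%. Over 0 to 20 weeks all three are zero.

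For power, 130 × 0.80 = 104 per arm remain, or 104 / 1.38 = 75.4 with the design effect. Under the 0 to 26 week scenario:

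| Assumed benefit | Mean difference | Power, design effect 1.38 | Power, no design effect |
|---|---|---|---|
| Full effect in everyone | 7.00 | 81.2% | 91.8% |
| Any session gives full benefit | 7 × 24/26 = 6.46 | 74.8% | 87.1% |
| Benefit rises evenly to three weekly sessions, then flat | 7 × 23/26 = 6.19 | 71.1% | 84.2% |

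In the last row, 23 = 22 weeks at full benefit + 2/3 + 1/3 for the two weeks of T in which two sessions and one session fit. The column without a design effect is shown because individuals are randomised within sites.

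**The case against.** The strongest reply is that this is an omission in a condensed article. Figure 2, which "presents the planned participant flow through enrolment and allocation, and details the intervention components and follow-up time points", is not shown, and neither is the full protocol; either may fix the start. The wording on session start is also permissive: it describes what generally happens and allows adjustment, so nothing tells a coach to hold back an allocated participant. The Post-intervention label suggests that delivery is meant to finish by week 12, and referral happens as discharge approaches, so 6 months may be an outer limit that few reach. Finally, in a pragmatic intention-to-treat trial low exposure is part of the effect being estimated. The pilot, logbooks, per-protocol set, dose–response analyses and 52-week RAS-DS would all help to expose or interpret the problem.

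Much of this stands. It makes the problem possible and not certain, and it leaves the number affected unknown. It does not remove the point. The stated default start is anchored to discharge, Table 1 presents itself as the full list of fixed and flexible elements, and it classes start timing as flexible. The supporting analyses change neither the primary contrast nor the single FIM time point.

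A reader might infer more: that the comparison is biased, or that the trial is underpowered. The documents support neither. Both arms are assessed on the same clock from baseline. The power figures depend on an enrolment pattern and a waiting rule that the article does not give, and the 7 points may already allow for partial uptake.

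**Conclusion.** The point holds as a mismatch between windows that the article states. At the earliest usual start, randomisation more than 24 weeks before discharge means no session by the primary assessment, and randomisation more than 22 weeks (weekly) or 20 weeks (fortnightly) before means less than the plan's own minimum dose. These limits need no assumption about enrolment.

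The consequence is possible dilution of the RAS-DS difference and some FIM ratings from people without experience of the intervention. The share affected is unknown. It is zero if early enrolees start at once, or if everyone enrols within 20 weeks of discharge and starts no later than the earliest usual point or at once. The fall in power from 81% to 75% or 71% is one illustrative scenario and should not be read as an estimate. The point should be fixed because the remedy is cheap; confidence is medium because the figure and the full protocol were not available.

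**What to change.** State one rule in Table 1: consent may be taken early, but baseline and randomisation take place only when the first session can be offered. With the first session at about week 0, three sessions fit by week 2 (weekly) or week 4 (fortnightly), and sessions stay close to discharge. Relabel the Table 2 column as 12 weeks post baseline.

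The cost is protocol wording and a site instruction, with no change to sample size, outcomes or analysis. An early referral who keeps the usual start would wait up to about 26 − 12 = 14 weeks between consent and randomisation, with somewhat slower accrual and some possible loss before randomisation.

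A fixed limit from randomisation to first session would avoid the wait, but it is a real trade-off because it moves sessions away from discharge. For someone enrolled at 26 weeks, an 8-week limit puts the first session at least 18 weeks before discharge and a 2-week limit at least 24 weeks before.

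If Figure 2 or the full protocol already sets a rule, repeat it in Table 1 and correct only the label.
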